***Major inclusion criteria include:***

- \* Age: 45-80 years
- \* ACR criteria for OA including Kellgren-Lawrence radiographic OA grades II-IV
- \* VAS pain score  $\geq 5/10$  within 48 hrs of the phone screen and visit 1 (Screening)
- \* Knee OA for a minimum of 12 months
- \* Need for daily pain medication to manage symptoms of OA

***Major exclusion criteria include:***

- \* Currently taking MAO inhibitors or any centrally acting drug for analgesia, depression
- \* Narrow angle glaucoma
- \* Uncontrolled hypertension
- \* Co-existing inflammatory arthritis, fibromyalgia or other chronic pain state.
- \* If a female, pregnant, trying to become pregnant, or lactating
- \* Major depressive disorder
- \* Substantial alcohol use or history of significant liver disease
- \* Use of MAO inhibitors, triptans, serotonin precursors (tryptophan)
- \* Use of potent CYP1A2 inhibitors, Thioridazine, and anti-depressants
- \* Diabetes, type 1 or type 2
- \* Condition in which the Investigator believes would interfere with the subject's ability to comply with study instructions, or might confound the interpretation of the study results or put the subject at undue risk
- \* MRI safety necessitates the exclusion of subjects having one or more of the following:
  - Metal fragments in the eye or face, or having worked previously in the metal industry
  - Implantation of any electronic devices such as (but not limited to) cardiac pacemakers, cardiac, defibrillators, and cochlear implants or nerve stimulators.
  - Surgery on the blood vessels of the brain
  - Claustrophobia (fear of enclosed places)
  - Piercings or tattoos
  - More than 250 lbs in weight

- Obvious brain abnormalities

### ***Efficacy Assessment***

Efficacy will be assessed primarily through the utilization of the WOMAC indices, specifically those regarding changes in pain, functionality, and stiffness in the knee. In addition, changes in VAS scores (from the sf-MPQ) could also be used to measure the drug's efficacy with regard to pain relief. The BDI scores could also be used to measure emotional or cognitive changes associated with the active drug, and thus act as an assessment tool in this regard.

### ***Safety Assessment***

The main ethical considerations are adverse effects of the active drug and subject safety for MRI scans. Regarding the first consideration, we will monitor adverse effects of the study drug by talking with participants at their clinical visits, collecting/recording any symptoms they mention, and reviewing participants' answers on the PRO battery questionnaires.

As for the second consideration, MRI safety is routinely implemented at Northwestern University brain imaging center, and there is an MRI screening form that must be completed and reviewed by trained personnel before every scan. If unrestrained iron or steel objects are accidentally brought near the MRI magnet, they can be pulled very quickly toward the magnet and can strike people in or near the magnet. Such an event is very unlikely, because precautions are taken to prevent such objects from being brought near the magnet. Participants are screened for iron or steel implants or clips from surgery, or metallic objects, such as shrapnel or metal slivers in their bodies, are excluded from the study if present. Dental fillings do not present a hazard.

A third issue is participant identity protection. All analyses and report of results will be based on using anonymized data. In addition, files of all participants will be confidential and will be available only to authorized study personnel.

### ***Statistical Analysis***

As soon as participants' MRIs are collected they are transferred to [name]'s lab where again we check for quality. Final data analysis cannot begin until all the repeat brain scans are collected, where we then follow procedures that we have used in the past. The correlative analyses require also getting all the pain questionnaire and drug use outcomes at study completion.

All participants' scans will be run through a quality control pipeline. Those participants whose scans are returned by the pipeline as poor in quality (e.g, they may have a low signal-to-noise ratio or too much movement), and verified to be so by qualified personnel, will *not* be included in data analysis concerning how the brain changes under the influence of the study drug. However, these participants' questionnaire data, medical history, and pain reportings may still be used in data analysis concerning drug efficacy.

Brain morphometry analysis follows our published procedures (Geha et al., Neuron. 2008; 60: 570. [name] et al., J. Neuroscience 24:10410, 2004). Briefly, we use three approaches to compare brain anatomy between groups (primary hypothesis) and correlate brain anatomical parameters with pain relief in the treatment arm (secondary hypothesis). For all subjects we

calculate whole-brain gray matter volume for the neocortex, normalized by skull size, and corrected for sex and age confounds. In the first approach, this value is then contrasted between treatment and placebo groups, which test the primary hypothesis for the whole-brain. In a second analysis, we perform voxel-based morphometry (VBM) where we calculate gray matter density for each voxel of gray matter (3 mm^3, about 20,000 voxels/brain). The VBM results are corrected for whole-brain volume, age and sex, and then contrasted between the groups. This contrast indicates what specific brain regions have changed in gray matter density and in what direction. In the third approach, we subdivide the neocortical gray matter into 80 morphological sections (Brodmann areas), correct them for age, sex, and whole brain volume, and contrast them between the two groups.

For the secondary hypotheses, the whole-brain volume, specific brain regions that show a change in VBM and Brodmann areas that show changes between groups are then regressed in the treatment group with pain measures. The sf-MPQ will be used to derive scalars for sensory and affective dimensions of osteoarthritis pain. Anxiety and depression traits will be determined by the BDI questionnaire, and intensity of pain will be assessed on a visual analog scale (0 - no pain, 10 - maximum imaginable pain), which is also part of the sf-MPQ. These characteristics will be related to brain morphometry and atrophy either by linear correlations or in multiple linear regression models with stepwise elimination. We do not expect to see a significant change with placebo treatment. However, we will regress the placebo pain measures with the brain regions identified as changing. If our assumption is correct, then this approach will distinguish between the biological effects of the treatment from the psychological (placebo) effects.

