### **Hypotheses:**

The primary hypothesis to be tested in the study is that subjects with chronic knee OA treated with Duloxetine over a four-month period will show decreased or arrested brain atrophy compared to subjects treated with placebo.

Secondary hypotheses are that in individual patients there will be a relationship between the magnitude of the analgesic effects of treatment and the magnitude of the change in brain atrophy. It is anticipated that there will be a correlation between pain relief by Duloxetine and changes in brain atrophy, whereas the degree of pain relief by placebo will not correlate with brain atrophy changes.

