For part two of the study, high-resolution anatomic brain images and functional brain scans are collected before and after four-months of treatment with duloxetine in 30 OA patients, in 30 OA patients who receive placebo, and in 25 healthy controls. Brain morphology is contrasted between these two time points, across the three groups, for overall neocortical gray matter volume and regional gray matter density changes. Pain relief, based on questionnaire outcomes and the MPQ's VAS, are then used as covariates in both patient groups to identify the effect size of magnitude of pain relief on restoration of brain grey matter. The procedures follow exactly our publications on the topic (Geha et al., *Neuron*. 2008; 60: 570. [name] et al., *J. Neuroscience* 24:10410, 2004).

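### The secondary hypothesis that pain relief tracks brain change on duloxetine but not on placebo is examined by separate within-arm regressions, with no comparison of the relation between arms

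*Protocol*

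**What the plan says.** - **Hypotheses.** The secondary hypothesis contrasts the arms. Pain relief on duloxetine is expected to correlate with change in atrophy, "whereas the degree of pain relief by placebo will not correlate with brain atrophy changes".
- **Statistical Analysis, duloxetine arm.** Whole-brain volume, and the regions and Brodmann areas that change between groups, "are then regressed in the treatment group with pain measures".
- **Statistical Analysis, placebo arm.** A second regression follows: "we will regress the placebo pain measures with the brain regions identified as changing".
- **Form of the model.** The pain and mood scores are related to the brain measures "either by linear correlations or in multiple linear regression models with stepwise elimination". The scores named there are the sf-MPQ sensory and affective dimensions, the BDI and the VAS.
- **Inference.** The section then concludes: "If our assumption is correct, then this approach will distinguish between the biological effects of the treatment from the psychological (placebo) effects".
- **Study Procedures, Part Two.** Pain-relief measures "are then used as covariates in both patient groups", to estimate how the size of relief affects gray matter. No term for a difference between arms is mentioned.

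**The concern.** The hypothesis is about a difference between arms, but the stated analyses estimate one relation at a time. A significant slope in one arm of 30 and a non-significant slope in another arm of 30 are compatible with equal slopes. A non-significant slope on placebo may only reflect limited power.

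The protocol attaches a mechanistic conclusion to this pattern, namely that drug biology has been told apart from placebo psychology. A reader of the trial report could be given that conclusion when the data do not distinguish the arms. The stepwise option, if used, adds a second route to a spurious relation, and the retained scores may differ between arms.

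**Working it through.** The protocol gives no alpha, power, correlation or SD for this analysis, so there is no figure of its own to reproduce. The nearby arithmetic in Sample Size Considerations, a drug arm three times the 10 patients of the two cited studies, is 3 × 10 = 30 and checks.

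**Inputs from the protocol.** 30 patients per arm (Part Two: "treatment with duloxetine in 30 OA patients, in 30 OA patients who receive placebo"); four named scores (Statistical Analysis).

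**Assumptions, not in the protocol.** Two-sided alpha 0.05; the same true correlation r and residual variance in both arms, with r from 0 to 0.6; normal data; stepwise elimination threshold 0.05. The predicted pattern is defined as a positive significant relation on duloxetine and a non-significant one on placebo.

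**1. How often equal relations produce the predicted pattern.** The arms are independent, so for r > 0 the probability is about power × (1 − power). At r = 0 only half of the significant results are positive, so it is (0.049 / 2) × (1 − 0.049). The last column comes from 200,000 simulated trials.

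| True r in both arms | Per-arm rate of significance | Product | Simulated |
|---|---|---|---|
| 0 | 0.049 | 0.023 | 0.023 |
| 0.2 | 0.186 | 0.186 × 0.814 = 0.151 | 0.151 |
| 0.3 | 0.371 | 0.371 × 0.629 = 0.233 | 0.233 |
| 0.4 | 0.606 | 0.606 × 0.394 = 0.239 | 0.237 |
| 0.5 | 0.827 | 0.827 × 0.173 = 0.143 | 0.142 |
| 0.6 | 0.956 | 0.956 × 0.044 = 0.042 | 0.043 |

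The peak is about 25%, near r = 0.36, where per-arm power is about one half. In the same simulations a direct test of the arm by pain-relief interaction rejected in about 5% of trials at every r. Among trials showing the predicted pattern at r = 0.2 to 0.5, the interaction was significant in only 9% to 14%.

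**2. An example.** The test statistic is t = r√(28 / (1 − r²)).

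- Duloxetine, r = 0.40: t = 2.31, p = 0.029.
- Placebo, r = 0.30: t = 1.66, p = 0.107.
- Difference by Fisher z: (0.424 − 0.310) / √(2/27) = 0.114 / 0.272 = 0.42, p = 0.67.

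This pair would look like the predicted asymmetry, although the data give no sign that the arms differ.

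**3. The stepwise option.** With four scores unrelated to the brain measure and 30 patients, backward elimination at 0.05 kept at least one score in about 19% of 4,000 runs. Four independent tests would give 1 − 0.95⁴ = 18.5%. Treating the arms as independent, a score is retained on drug and none on placebo in about 0.194 × 0.806 = 16% of cases per brain measure.

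**4. What a direct comparison can detect.** Power = Φ(difference in Fisher z / 0.272 − 1.96). For 0.5 versus 0: Φ(0.549 / 0.272 − 1.96) = Φ(0.06) = 0.52. The same formula gives 0.34 for 0.4 versus 0 and 0.72 for 0.6 versus 0. For 80% power, about 91, 56 and 36 patients per arm would be needed for 0.4, 0.5 and 0.6 versus 0.

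**The case against.** Several points can fairly be made for the protocol.

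- **No decision rule is written.** The protocol never says that significance on drug with non-significance on placebo counts as confirmation, and a reader might wrongly infer that it does. The simulations examine the natural reading of the two regressions, not a stated rule. What remains is that the protocol draws a between-arm inference and offers no between-arm comparison to support it.
- **Stepwise elimination is not fixed.** It is one of two options, so the claim cannot be said to rest on it. The main problem is the same with simple correlations.
- **The pattern is rare if there is no relation in either arm.** With simple correlations it appears in about 2% of trials at r = 0. The larger figures need a real, moderate relation in both arms. A reader might infer that pure noise often produces the predicted result; outside the stepwise option, it does not.
- **The inference is conditional.** The protocol makes it depend on its assumption about placebo, and Background and Rationale concedes that the assumption that placebo does not reverse atrophy may be false. But a non-significant result in 30 patients cannot establish the assumption, so the condition does not rescue the conclusion.
- **Part Two may describe a joint model.** Using pain relief as a covariate in both patient groups need not contradict the Statistical Analysis section. It still names no term for a difference in slopes.
- **The study is exploratory, and the statistical analysis plan is not at hand.** Model details may properly be left to that plan. Here, however, the protocol itself states the method and the conclusion to be drawn. Sample Size Considerations also expects adequate power for the secondary hypotheses, although it admits that the sample size has no statistical justification.

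The primary hypothesis rests on a direct contrast of drug with placebo and is not affected.

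**Conclusion.** The point holds in limited form. The protocol states a between-arm hypothesis, analyses each arm separately, and claims to tell biological from placebo effects without comparing the arms. If significance is read arm by arm, equal relations give the predicted pattern in about 14% to 24% of trials for correlations of 0.3 to 0.5, and in about 2% and 4% at 0 and 0.6. These figures rest on 30 evaluable patients per arm and an assumed two-sided alpha of 0.05. The 19% for the stepwise option also assumes a 0.05 elimination threshold and no true relation.

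A reader might infer that an interaction test would settle the mechanism. It would not: pain relief is measured after randomisation, so even a significant interaction would not alone separate biological from psychological effects. The matter should be corrected, but it concerns a secondary hypothesis only.

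**What to change.** 1. For this claim, fit one model across both randomised arms: change in the brain measure on arm, change in one named pain measure, and arm by pain-change, with the age and sex adjustment already planned. The sf-MPQ VAS is a suitable choice, since Study Design already names it for the secondary correlations.
2. Base any statement that the relation is present on drug but not on placebo on the interaction estimate and its 95% confidence interval. Show the slope in each arm with its interval.
3. Drop stepwise elimination for this claim, and label models that use the other scores as exploratory.
4. Reword the sentence on biological versus psychological effects so that it claims an association that differs, or does not differ, between arms, and no more.

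The cost is a change of wording in the protocol and analysis plan and a small amount of analysis; no new data are needed. The drawback is that power is modest, about 52% for correlations of 0.5 versus 0, so the claim may not be supported. The protocol should say so.

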The issue of atrophy due to pain in relation to changes due to aging warrants further clarification. In the 4 months of treatment all subjects should have atrophy due to aging, about  $2.5 \text{ cc} \times 0.3 = 0.75 \text{ cc}$ . On the other hand the OA cumulative atrophy over the years seems to be proportional to the number of years a given subject has had the condition. If we assume on average that the mean OA duration is 5 years, then the atrophy due to chronic pain should be about  $1.5 \text{ cc} \times 5 = 6.0 \text{ cc}$ . Therefore, in a subject where the OA pain completely disappears with treatment, that subject has the potential of exhibiting a reduction in atrophy of 6.0 cc minus the increased atrophy due to aging of 0.75 cc. Moreover, we assume that placebo responses will not induce reversal of atrophy because placebo mainly reflects attentional and motivational states of the person. There is likelihood that this assumption may not be true. Even in the latter case as we expect placebo to decrease pain less than the real drug treatment, we should still observe smaller changes in atrophy by placebo.

We consider the brain atrophy in chronic pain as an overall marker of the extent of peripheral, spinal cord, and brain reorganization a subject has developed with living and suffering with the condition. Animal models of chronic neuropathic and inflammatory pain repeatedly show that peripheral and spinal cord nociceptive transmission is dramatically changed, leading to

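### Separate regressions of brain change on pain relief in each arm cannot show that the relation differs between duloxetine and placebo; the slopes need a direct comparison

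*Protocol*

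**What the plan says.** The secondary hypotheses have two parts. The first, in the Hypotheses section, is a plain relationship within individual patients between analgesic effect and brain change. Study Endpoints and Anticipated Results repeat it in that form. The second is a contrast between arms. The Hypotheses section expects a correlation on drug and none on placebo, and words the pair as follows: "pain relief by Duloxetine and changes in brain atrophy, whereas the degree of pain relief by placebo will not correlate with brain atrophy changes".

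The analysis stated for this works one arm at a time. The lead-in to Statistical Analysis places the correlation with relief in the treatment arm and labels it the secondary hypothesis. Later in that section, whole-brain volume and the regions that show change "are then regressed in the treatment group with pain measures". For placebo the text says "We do not expect to see a significant change with placebo treatment" and then "we will regress the placebo pain measures with the brain regions identified as changing". It closes with the claim that, if the assumption is correct, "this approach will distinguish between the biological effects of the treatment from the psychological (placebo) effects".

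Two other places bear on this. In the detailed procedures for Part Two: "Pain relief, based on questionnaire outcomes and the MPQ's VAS, are then used as covariates in both patient groups", with the aim of estimating the effect size of relief. In Background and Rationale, on the assumption that placebo does not reverse atrophy: "There is likelihood that this assumption may not be true". In that case smaller changes on placebo are expected.

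**The concern.** To say that a relation exists on drug and not on placebo is to say that two slopes differ. The protocol describes two regressions and no comparison of them. If the closing claim is read from one regression that reaches significance and one that does not, a placebo slope that was simply missed in 30 patients would count as support for a drug-specific biological effect.

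The condition attached to the claim does not supply the comparison. The nearest assumption is that placebo produces no significant change. That concerns the mean, and a group with no significant mean change can still have the same slope of brain change on relief. The alternative that the protocol itself raises, less relief and smaller brain changes on placebo, is compatible with one common slope.

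At stake is the secondary conclusion that relief from duloxetine goes with brain recovery and relief from placebo does not.

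**Working it through.** **Inputs from the protocol.** 30 patients on duloxetine and 30 on placebo in phase II (Number of Subjects). The protocol gives no significance level, correlation or spread of relief for this analysis, so it has no figure to reproduce. Sample Size Considerations says that the sample size has no statistical justification.

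**Assumptions.** Two-sided 5% tests; true correlation rho between relief and brain change of 0.3 to 0.6; same residual variance and same standard deviation of relief in both arms; one outcome, one predictor, no covariates.

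**Step 1: what a null placebo result can exclude.** With n = 30 the critical t on 28 df is 2.048, so |r| must exceed 2.048/√(2.048² + 28) = 0.361. An observed r of 0 has a 95% interval of ±tanh(1.96/√27) = ±0.36. Moderate correlations remain compatible with a non-significant result.

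**Step 2: chance of the misleading pattern when the slopes are identical.** If each arm has power p, the arms are independent and the pattern (duloxetine significant, placebo not) has probability p(1 − p). By the Fisher approximation, p = Φ(atanh(rho)·√27 − 1.96) plus a negligible opposite tail. At rho = 0.4: 0.4236 × 5.196 = 2.201; p = Φ(0.241) = 0.595; p(1 − p) = 0.241. Simulation with t tests (60,000 trials per value) agrees:

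| rho | Fisher p(1 − p) | Simulated pattern |
|---|---|---|
| 0.3 | 0.231 | 0.233 |
| 0.4 | 0.241 | 0.236 |
| 0.5 | 0.151 | 0.140 |
| 0.6 | 0.048 | 0.044 |

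A direct test of the slope difference (t on 56 df, critical value 2.003, pooled residual variance) wrongly favours duloxetine in 2.3% to 2.7% of these trials, as its 2.5% per tail implies.

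**Step 3: an example.** Observed r = 0.40 on duloxetine gives p = 0.029; r = 0.30 on placebo gives p = 0.107. That fits the anticipated pattern. The test of the difference is z = (0.4236 − 0.3095)/√(2/27) = 0.114/0.272 = 0.42, p = 0.67.

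**Step 4: what the direct comparison can deliver.** Suppose the placebo slope is truly zero and the spread of relief is equal:

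| rho on duloxetine | Power of slope difference | Separate tests show the pattern |
|---|---|---|
| 0.3 | 21% | 35% (0.37 × 0.95) |
| 0.4 | 36% | 58% |
| 0.5 | 56% | 78% |
| 0.6 | 78% | 91% |

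At rho = 0.5 the 95% half-width is about 2.003 × √(0.75 × 2/29) = 0.46 standard deviations of brain change per standard deviation of relief. An observed difference of 0.5 would only just exclude zero (0.50 − 0.46 = 0.04).

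**The case against.** Several points on the other side are fair.

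- **The secondary hypothesis is mostly a plain correlation.** A reader might infer that it goes untested as a whole. It does not: the within-arm regression addresses the form given in the first sentence of the secondary hypotheses, in Study Endpoints and in Anticipated Results. Only the between-arm anticipation and the closing claim lack support.
- **The decision rule is inferred.** The protocol nowhere says that a significant drug slope with a non-significant placebo slope is the criterion. Its one use of the word significant in that passage refers to change on placebo, not to a slope. This stands as a limit. But the protocol names no other route from the two regressions to the claim.
- **Relief as a covariate in both patient groups might mean one joint model.** It might, and the analysis plan is not shown, so it cannot be said that the slopes will never be compared. Yet a common covariate slope would not compare the arms, and the stated aim there is an effect size for relief.
- **The simulation is simpler than the plan.** It uses one unselected outcome and one predictor. The plan names several pain measures, possible stepwise elimination, and regions already identified as changing. The figures illustrate the logic and do not predict this trial's error rate.
- **Larger figures are available.** If relief varied half as much on placebo, the pattern would arise in 32% to 56% of trials. Sample Size Considerations assumes less relief on placebo, not a smaller spread, so the document does not support relying on those figures.
- **The study calls itself exploratory.** That excuses low power. It does not license a claim that the approach will distinguish two kinds of effect.

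**Conclusion.** The point holds for the between-arm part of the secondary hypothesis and for the closing claim of Statistical Analysis. The issue is not detail left to an analysis plan: the protocol states both a procedure and a conclusion, and the conclusion does not follow from the procedure.

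With identical slopes and equal spread of relief, the misleading pattern has a probability of about 4% to 24% for rho between 0.6 and 0.3, against 2.5% for a direct slope test. This rests on an assumed 5% level, assumed correlations and the inferred reading of the two regressions. At rho = 0.6 the problem is small.

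A reader might go further and conclude that the comparison of duloxetine with placebo on brain volume is compromised. It is not: that randomised contrast does not use relief. Nor would a clear slope difference establish a biological mechanism, because relief is measured after randomisation. The change is worth making, but it concerns a secondary conclusion only.

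**What to change.** 1. For the change in whole-brain neocortical volume, and for each region carried into the placebo regression, fit one model in the 60 randomised patients: brain change on relief, arm and arm-by-relief, with the age and sex terms already planned, plus whole-brain volume for the regions.
2. Report the slope difference with its 95% confidence interval. Treat the regional results as descriptive. State that the relation differs by arm only if the whole-brain interval excludes zero.
3. Keep the within-arm regressions as description; they continue to serve the plain correlation part.
4. Replace the closing claim with a sentence such as: *A non-significant slope on placebo is not evidence of no relation; and since relief is measured after randomisation, a difference in slopes shows an association, not a biological as opposed to a psychological cause.*

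The change needs no further patients, visits or data. The price is power: the slope difference would be detected in roughly one trial in five at rho = 0.3 and in fewer than four in five at rho = 0.6, even with no relation on placebo. The likely result is an estimate with a wide interval, which suits a study described as exploratory.
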